Neurological	• Ischemic cerebrovascular accident • Hemorrhagic cerebrovascular accident	• Epileptic seizure • Cerebral thrombophlebitis
Surgical	• Recurring diaphragmatic paralysis/paresis • Definitive AV block with device • Acute hemorrhaging requiring revision surgery	• Cardiac tamponade • Unplanned revision surgery • Chylothorax

There is no consensus regarding the optimal age for surgery in terms of morbidity and neurodevelopmental outcomes, and its definition is a real challenge. Importantly, at the present time, there are no established rules for determining the timing of surgery in our department. For the most common CHD types, the TGA are corrected during the first ten days of life. There is a more pronounced degree of variation for HLHS. This common practice won't be changed for our observational study.

Our aim is to determine the relationship between surgical timing and long-term neurodevelopmental outcomes for various types of complex CHD. Similarly to Anderson et al. (15) with postoperative morbidity, we aim to determine a cut-off point for surgical timing that will improve neurodevelopmental outcomes. For each type of CHD, we aim to determine a cut-off for surgical timing based on postoperative morbidity and neurodevelopmental outcomes. We hope that our findings will contribute to the development of surgical timing guidelines in the future.

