### Main objective

1.2.

The main objective of this study is to assess the correlation between age at surgery (days of life) of neonates with complex CHD and neurodevelopmental outcomes at 24 months, assessed by the scores obtained on the subscales of the Bayley Scale of Infant and Toddler Development®, Fourth Edition® (Bayley-IV test) exploring motor skills, cognition, and language (18).

Our aim is to determine the optimal threshold for the age at surgery that discriminates delayed neurodevelopment / normal neurodevelopment according to the main criterion, i.e. neurodevelopment at 24 months according to the Bayley-IV scale (score <80 vs. ≥80).

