#### Sample size

3.1.1.

Two previously published studies that reported a significant correlation between age at surgery and the incidence of WMIs included 26 and 37 patients, respectively (7, 8). Based on the active file of patients with complex CHD operated on each year in Cardiac Surgery at the La Timone Enfants Hospital, the total number of subjects included will be 100. With this number of 100 included patients and according to the values of (i) a 5% bilateral alpha risk and (ii) 80% statistical power, we estimate the minimum correlation coefficient between age at surgery and Bayley-IV test scores as 0.39.

According to the same hypotheses (5% bilateral alpha risk and 80% statistical power), and based on the intended number of patients recruited for each (Clancy) CHD subtypes, the minimum correlation coefficient that could be highlighted between age at surgery and Bayley-IV test scores is:
*r* = 0.38 for class I, two-ventricle heart without arch obstruction (*n* = 50)*r *= 0.65 for class II, two-ventricle heart with arch obstruction (*n* = 15)*r* = 0.76 for class III, single ventricle heart without arch obstruction (*n* = 10)*r* = 0.53 for class IV, single ventricle heart with arch obstruction (*n* = 25)”

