#### Main analysis

3.1.2.

The analysis of the main objective will be based on the evaluation of the correlation between the age at surgery (in number of days of life) and the main analysis criteria selected, namely the neurodevelopmental outcomes at 24 months assessed using the scores obtained on the Bayley-IV scale. The analysis will be conducted for the entire cohort and separately for each type of complex CHD to define the optimal age for surgery for each complex CHD type. To do this, Pearson's correlation coefficient will be estimated with a 95% confidence interval if the application conditions are met (otherwise, the non-parametric Spearman's rank correlation coefficient will be estimated with a confidence interval of 95%). A ROC curve will be plotted to curve to determine (according to Youden's method) the optimal threshold for the age at surgery that discriminates delayed neurodevelopment / normal neurodevelopment according to the main criterion, i.e. neurodevelopment at 24 months according to the Bayley-IV scale. The first secondary endpoint based on the AIMS scores at 4 months and 12 months will be analyzed using the same previously described strategy. The next secondary endpoint based on the clinical assessment by the child neurologist (neurodevelopment considered normal vs. abnormal) at 4 months, 12 months, and 24 months will be analyzed using a comparison test for quantitative data. A Student's t-test will be used if the application conditions are met; otherwise, the non-parametric Mann-Whitney test will be used.

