## Discussion

4.

The correlation between surgical timing and long-term neurodevelopmental outcomes in children with complex CHD has not been fully studied. Moreover, currently, there is no consensus regarding the optimal surgical timing for neonates with complex CHD. Our study will allow us to define the optimal time-window within the neonatal period to perform cardiac surgery to reduce postoperative morbidity (i.e., postoperative complications) and optimize the neurodevelopment of infants with complex CHD. We hope our work will facilitate the evaluation of the risk/benefit ratio of the chosen therapeutic strategy.

A better understanding of the mechanisms underlying neurodevelopmental disorders in this population will allow the identification of other modifiable risk factors and the development of new prevention and screening strategies to improve the neurodevelopment and overall health of children and adults.

An added challenge for this field is the recruitment of patients with various types of CHD to define a general optimal age for cardiac surgery and an optimal age for each CHD type and not only for TGA and HLHS, which have been studied in more depth.

Moreover, the patients in our study will receive a neurodevelopmental follow-up at 4 months, 12 months, and 24 months. They will benefit from early screening for neurodevelopmental disorders with an orientation toward adapted rehabilitation structures, thereby supporting improvements in their overall neurodevelopmental outcome. The aim is to extend this treatment process to all patients with complex CHD who undergo surgery in their first weeks of life. This project, initially internal in hospitals in Marseille, could be extended with the collaboration of pediatric cardiology and neurology teams across France.

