## Limitation

5.

As Complex CHD are characterized by their heterogeneity, the monocentric nature of our protocol study may be considered a limitation, as well as the relatively low number of participants to be recruited (*n* = 100). This preliminary work may allow us to define an optimal surgery timing only for those CHDs that recruit frequently (e.g., TGA, aortic arch hypoplasia). The extension of this project to other pediatric cardiology and neurology teams in France will enable more reliable results to be obtained.

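### The optimal age at surgery for each CHD type rests on an unadjusted Youden cut-off that is too unstable at the planned class sizes and is almost always returned, even with no association

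*Protocol article*

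**What the plan says.** Section 1.2 (Main objective) sets the target: "Our aim is to determine the optimal threshold for the age at surgery that discriminates delayed neurodevelopment / normal neurodevelopment", with delay defined as a Bayley-IV score below 80. Section 3.1.2 (Main analysis) gives the method: "A ROC curve will be plotted to curve to determine (according to Youden's method) the optimal threshold for the age at surgery". The same section runs the analysis on the whole cohort and "separately for each type of complex CHD to define the optimal age for surgery for each complex CHD type". The Introduction repeats the aim: "For each type of CHD, we aim to determine a cut-off for surgical timing based on postoperative morbidity and neurodevelopmental outcomes".

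Section 3.1.1 (Sample size) plans 50, 15, 10 and 25 infants in classes I to IV; the 10 are "for class III, single ventricle heart without arch obstruction". Table 3 lists 16 diagnoses within these four classes, seven of them in class III.

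The Discussion says: "Our study will allow us to define the optimal time-window within the neonatal period". The Limitation section says the work "may allow us to define an optimal surgery timing only for those CHDs that recruit frequently". The Conclusion returns to timing for each type.

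Two other elements matter here. Section 3.1.2 also estimates a Pearson or Spearman correlation with a 95% CI. Section 3.1.3.4 plans multivariate linear regression of the Bayley-IV score on age at surgery plus prognostic factors chosen in advance, reported as adjusted coefficients with 95% CIs.

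**The concern.** Youden's index answers a classification question: which age best sorts this sample into delayed and normal. That need not be the age at which outcome is best, and it says nothing about what would happen if a given infant were operated on earlier.

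The threshold step is also crude. The Introduction says that very low weight or hemodynamic instability can delay surgery. It also says that TGA is corrected within the first ten days while HLHS timing varies more. A whole-cohort cut-off can therefore reflect the mix of lesions and how sick the infants were. The regressions in 3.1.3.4 adjust for such factors, but they yield coefficients and no threshold.

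The sample maximum of Youden's index is biased upwards, and its location is poorly determined in small groups. The plan attaches no condition to reporting it. The Conclusion expects the results to help develop timing guidelines, so an unstable number could be read as a surgical-age threshold.

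**Working it through.** **Inputs from the article.** Class sizes 50, 15, 10 and 25 (total 100); two-sided 5% alpha and 80% power (3.1.1); delay = Bayley-IV below 80 (1.2); surgery within the first 2 months of life (2.2). The article states no precision for the cut-off. Its only related figures are minimum detectable correlations, so these come first.

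**The plan's own figures.** Fisher's z: r = tanh((1.960 + 0.842)/√(n-3)).
- n=50: 0.387 (stated 0.38)
- n=15: 0.669 (0.65)
- n=10: 0.785 (0.76)
- n=25: 0.535 (0.53)
- n=100: tanh(2.802/√97) = 0.277 (stated 0.39)

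With a small-sample correction the class figures become 0.384, 0.657, 0.770 and 0.528, within about 0.01 of those stated. The whole-cohort figure does not reproduce. That is a separate matter. It is used here only to choose the scenario: -0.28 is about the weakest correlation that 100 infants can detect with 80% power.

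**Assumptions not in the article.** Age at surgery is either log-normal (median 10 days, log SD 0.6; 5th to 95th percentile 3.7 to 26.8 days) or uniform on 1 to 60 days. The share scoring below 80 is 25% or 50%. The Introduction says more than half of these children have a neurodevelopmental disorder, which is an imperfect proxy for a score below 80. The rule is that age ≥ c predicts delay, with c maximising J = sensitivity + specificity - 1.

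**No association (true J = 0).** A cut-off with apparent J above 0 is returned in about 85 to 96% of samples of 10 to 25 in which a ROC can be drawn. At n=10 the mean apparent J is about 0.33 to 0.39, or about 0.31 with log-normal ages rounded to whole days and 50% delayed.

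**True correlation -0.28, 25 to 50% delayed.** 5th to 95th percentile of the cut-off, in days:

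| n | log-normal age | uniform age |
|---|---|---|
| 10 | 5-28 | 10-58 |
| 25 | 5-24 | 11-56 |
| 100 | 6-19 | 13-51 |

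Simulation error and rounding of ages move these limits by a day or two. At n=10 and n=25 the cut-off spans most of the assumed age range. At n=100 it is narrower but still wide.

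**Number of delayed infants in class III (n=10).** P(at most one) = (1-p)^10 + 10p(1-p)^9.
- p=0.10: 0.349 + 0.387 = 0.74
- p=0.25: 0.056 + 0.188 = 0.24
- p=0.50: 0.001 + 0.010 = 0.01

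The ROC is undefined if no infant, or every infant, is delayed. At p=0.10 the chance that none is delayed is 0.9^n: 35% at n=10, 21% at n=15 and 7% at n=25.

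**A single cut and a window.** If risk were U-shaped over days 1 to 20 with its minimum at day 10.5 (purely an assumption), the Youden cut-off at n=10,000 settles near day 17. That is a point on the late limb. It is neither the minimum nor the early limit of a window.

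**The case against.** The strongest reply is that the plan does not rest on the cut-off alone. Section 3.1.2 leads with a correlation on the continuous score with its CI, so a null association would be visible beside any threshold. Section 3.1.3.4 already regresses the continuous score on age with adjustment. A reader might infer that the plan has no adjusted analysis or discards the continuous score throughout. It does neither; the loss is confined to the threshold step. That step, however, is where the optimal age comes from, and neither other analysis supplies an adjusted threshold.

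A reader might also infer that a cut-off is always returned. It is not: the ROC can be undefined, and J can be 0. Almost always is the accurate wording.

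A reader might infer that the method cannot serve the stated objective at all. Section 1.2 asks for a threshold that discriminates, which is what Youden estimates, and section 1.1 hypothesises that earlier is better. The difficulty with a window arises only if risk is not monotone in age. The Introduction's remark that small or unstable infants may be too risky to operate on hints at this but does not establish it. This part is secondary.

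Finally, the article calls the work preliminary and says extension to other centres is needed for more reliable results. The Conclusion mentions a later interventional study, but does not say that this cut-off would set its threshold. An analysis plan that is not shown could add an interval for the cut-off. That would show the instability without removing it or adding adjustment.

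**Conclusion.** The point holds. The crude Youden cut-off is a poor basis for an optimal age at surgery for each CHD type: it is unadjusted, almost always returned even under no association, and at 10 to 25 infants it can fall almost anywhere in the age range. The problem is less severe but not absent at n=100.

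Instability appeared under every age distribution and delay rate tried. The limits in days did not stay fixed: they largely mirror the assumed ages and should not be read as forecasts for any class. Likewise, the chance of at most one delayed infant in class III runs from 1% to 74% over delay rates of 50% down to 10%, so no single value should be quoted alone.

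The contradiction within the article needs no assumption. The Limitation section restricts what may be definable to frequent lesions, while the Introduction, section 3.1.2 and the Conclusion keep the promise for each type.

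**What to change.** Base the conclusion about age and outcome on the linear regression in 3.1.3.4: continuous Bayley-IV score on age at surgery, adjusted for CHD class and preoperative severity. Enter age as a restricted cubic spline with three knots, and show the fitted curve with its 95% CI.

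If a Youden cut-off is kept, label it exploratory. Restrict it to the whole cohort and to groups large enough to support it. Report the AUC with its CI and a bootstrap CI for the cut-off, and give no cut-off when the AUC interval includes 0.5.

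Bring the Introduction, section 1.2, section 3.1.2, the Discussion and the Conclusion into line with the Limitation section.

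The cost is more than wording in the analysis section. The threshold part of the main objective becomes exploratory, and cut-offs are no longer promised for the small classes. No extra data are needed: CHD type and the preoperative variables are already collected under section 2.9, and the spline adds one parameter to a linear age term.

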##### Morbidities

3.1.3.2.

The correlation between age at surgery (in number of days of life) and the occurrence of at least one of the elements of post-op morbidity (yes vs. no) will be assessed by describing and comparing age at surgery according to the presence and absence of a morbidity criterion. A comparison test for quantitative data will be used. The Student's t-test will be used if the application conditions are met; otherwise, the non-parametric Mann-Whitney test will be used. This analysis will be conducted with consideration for each element of morbidity in isolation.

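### Both main analyses can include only children alive and tested at 24 months, and no endpoint in the article counts death, so the optimal age for surgery needs a survivors-only label and death-inclusive results beside it

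*Protocol article*

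**What the plan says.** The Protocol article's Main analysis section fixes the main criterion, "namely the neurodevelopmental outcomes at 24 months assessed using the scores obtained on the Bayley-IV scale". The estimator follows: "Pearson's correlation coefficient will be estimated with a 95% confidence interval if the application conditions are met", with Spearman's coefficient as the fallback.

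The same section adds an ROC curve with Youden's method to find "the optimal threshold for the age at surgery that discriminates delayed neurodevelopment / normal neurodevelopment". The Main objective section gives the two outcome states: "neurodevelopment at 24 months according to the Bayley-IV scale (score <80 vs. ≥80". The analysis is run overall and by type of heart disease "to define the optimal age for surgery for each complex CHD type".

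Other outcomes feed the timing question. The Introduction states that "we aim to determine a cut-off for surgical timing based on postoperative morbidity and neurodevelopmental outcomes". The Morbidities analysis uses "the occurrence of at least one of the elements of post-op morbidity (yes vs. no", with the elements taken from Table 2. That table lists cardiac arrest, extracorporeal membrane oxygenation, tamponade and many other events, but not death. Death is also absent from the secondary objectives, the regression outcomes and the Limitation section.

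Three further statements matter:
- The Procedure overview places recruitment before surgery and follows each child for 24 months.
- The Exclusion criteria remove infants who lack a preoperative or postoperative MRI, including for poor health.
- The Discussion says the study will "define the optimal time-window within the neonatal period to perform cardiac surgery" and help weigh risk against benefit. The Conclusion looks ahead to timing guidelines.

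**The concern.** A Bayley-IV score at 24 months exists only for a child who is alive and tested then. A death drops out of the correlation, and in the threshold analysis it is neither delayed nor normal. No endpoint described in the article picks it up elsewhere. Infants are enrolled before surgery, and the planned cohort includes 25 infants in Clancy class IV and 10 in class III (single-ventricle hearts), so deaths among enrolled infants are to be expected.

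The conclusion, however, is worded as an optimal age for surgery and not as a description of development in survivors. If mortality varies with age at surgery, the age that looks best among survivors need not be the age with the fewest bad outcomes overall. The article makes such variation plausible, because its Introduction says that low weight or instability can delay an operation.

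The MRI exclusion adds to the selection. An infant who dies before the postoperative scan may leave the cohort under that rule, and then would not be seen even in a simple count of deaths among analysed patients.

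**Working it through.** **What needs no assumption.** Setting the sections side by side, the correlation needs a score, the threshold needs a score on one side of 80, and no other listed outcome includes death. Both main analyses are therefore survivors-only as written.

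**What needs assumptions.** The article gives no mortality rate, so there is no figure of its own to reproduce on this point. All rates below are assumed.

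**Step 1: two age bands.** Let d be the proportion who die and p the proportion delayed among survivors. Then death or delay = d + (1 − d) × p. Take p = 25% early and 35% late, so the survivors' comparison always favours early by 10 points.

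| Deaths early / late | Death or delay, early | Death or delay, late | Ranking |
|---|---|---|---|
| 5% / 5% | 0.05 + 0.95 × 0.25 = 28.8% | 0.05 + 0.95 × 0.35 = 38.2% | unchanged |
| 10% / 5% | 0.10 + 0.90 × 0.25 = 32.5% | 38.2% | unchanged |
| 15% / 5% | 0.15 + 0.85 × 0.25 = 36.2% | 38.2% | unchanged |
| 20% / 5% | 0.20 + 0.80 × 0.25 = 40.0% | 38.2% | reversed |
| 25% / 5% | 0.25 + 0.75 × 0.25 = 43.8% | 38.2% | reversed |
| 5% / 20% | 28.8% | 0.20 + 0.80 × 0.35 = 48.0% | unchanged, gap widens to 19 points |

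With 5% late deaths, the ranking turns where d + (1 − d) × 0.25 = 0.3825, that is d = 0.1325 / 0.75 = 17.7%.

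**Step 2: correlation.** Large-sample simulation. The standardised score has coefficient −0.2 on standardised age and −0.5 on an unobserved frailty. Death is logistic, with odds ratio 3 per SD of frailty. Overall mortality is 5%, 10% or 20%. The entries are rank correlations and reproduce to about 0.01 on re-running.

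| Odds ratio for death per SD later | Survivors only | Death ranked worst |
|---|---|---|
| 0.5 (earlier surgery, more deaths) | −0.20 / −0.21 / −0.22 | −0.13 / −0.08 / +0.01 |
| 1 (unrelated) | −0.19 at each rate | −0.18 / −0.16 / −0.13 |
| 2 (later surgery, more deaths) | −0.18 / −0.17 / −0.16 | −0.21 / −0.22 / −0.25 |

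The first row implies a steep gradient. Deaths in the earliest against the latest quarter of ages are about 9% v 2%, 18% v 4% and 32% v 10%. With a milder odds ratio of 0.8, the death-inclusive correlation stays negative, between −0.16 and −0.08.

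**Step 3: threshold.** Simulation with 5,000 infants per run. Earlier surgery improves scores (r = −0.21 before deaths), and deaths are about 25% at 7 days or younger and 8% later. Among survivors the AUC of age for delay is 0.62, with delay 11% early and 21% late. Counting death as a bad outcome, the AUC is 0.50 and the rates are 33% early and 27% late. With mortality unrelated to age and no effect on score, the AUC is 0.50 either way.

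**The case against.** Several counter-arguments have force.

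**Scope.** Handling of missing 24-month scores and sensitivity analyses are commonly left to an analysis plan that is not shown. That covers the technique. It does not cover the outcome states, which this text fixes as below 80 or not, nor the list of endpoints, which leaves death out. The statement has to stay at no endpoint described in the article.

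**The stronger reading.** A reader might infer that the plan will recommend an age at which more infants die. The documents do not support this. They give no mortality figure, and reversal needs a steep excess of deaths with earlier surgery. The Introduction's own evidence leans the other way: it cites lower major morbidity with early arterial switch and higher morbidity with later surgery for left-ventricle hypoplasia. If mortality follows that pattern, the survivors' result understates the association and does not mislead on direction.

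**Estimand.** Development among survivors is a legitimate question. The survivors' correlations in step 2 stay between −0.16 and −0.22 against a true coefficient of −0.20. Part of the shift when death is ranked worst is a change of question: even with mortality unrelated to age, it moves the value from −0.19 to between −0.18 and −0.13. This supports keeping the survivors' analysis under a clear label.

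**Morbidity as a proxy.** Some deaths may follow a listed morbidity and so be counted there. The death itself would then weigh no more than any other single element.

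**Purpose.** The article calls the work preliminary. It still ties the result to risk and benefit, to guidelines, and to a later interventional study that would lower age at surgery.

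**Conclusion.** The point holds in a limited form. As described, the correlation and the Youden threshold are survivors-only, death counts in no described endpoint, and the MRI exclusion can hide further early deaths. That much follows from the text without assumptions, and it does not match the claim to define an optimal age.

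The numerical consequence is unknown. If mortality does not depend on age at surgery, distortion of the survivors' estimate is slight. If later surgery carries more deaths, the survivors' result is conservative. A reversal requires, in the two-band example, early deaths above about 18% against 5% late. These statements rest on assumed mortality, an assumed frailty effect and assumed delay rates. The documents show neither that the survivors' answer is wrong nor in which direction it would err. The change is worth making because the conclusion cannot be read safely without the deaths beside it.

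**What to change.** 1. Keep the survivors' correlation and threshold, and label both as applying to children alive and tested at 24 months.
2. Tabulate deaths before 24 months by age at surgery and Clancy class for all enrolled and operated infants, including those excluded for a missing MRI. Without that last group the table would miss early perioperative deaths. Deaths before surgery have no age at surgery and need a separate line.
3. Report beside the main result a Spearman correlation with death ranked below the lowest Bayley-IV score, and a threshold analysis with the outcome death or Bayley below 80.
4. Interpret any optimal-age statement in the light of both sets of results. A formal rule that the signs must agree is not advised: with 100 children the standard error of r is about 1/√97 = 0.10, so signs can differ by chance when the correlation is small.

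The cost is wording and two supplementary analyses. No new visits are needed, and vital status should be known from the planned follow-up. The downside is that a death-inclusive result mixes survival with development, so it supplements the survivors' analysis and does not replace it.
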